#### Usual Care Group (UCG) Only

Following final measurements, each UCG participant will receive the same package of interventions offered to the PCG at baseline. UCG participants will receive follow-up pharmacy services two months after the 'Final project visit'. The pharmacist will:

• measure patient's BP (as described above);

• review patient's home BP recordings;

• review patient's BP measurement techniques;

• discuss adherence issues; and

• refer when needed (e.g. persistent uncontrolled BP).

### Data analysis

Participant characteristics in the UCG and PCG will be compared at baseline. Paired t-tests and/or Wilcoxon Signed Rank test will be used to compare changes in total scores on the Morisky scale, TABS and MedsIndex between the PCG and the UCG at baseline and six months. MedsIndex scores will be compared using paired t-tests and/or Wilcoxon Signed Rank test in the UCG and the HCG at six months.

Baseline data will be used to identify factors associated with suboptimal adherence in the whole study population. Significant factors in univariate analysis (chi-square, Mann-Whitney U test and Student's t-test) will be further tested in multivariate analysis (linear regression) to identify independent predictors of nonadherence/nonpersistence in the study population. To adjust for cluster randomisation, a pharmacy variable will also be included in the multivariate models.

An economic evaluation will also be carried out and will be reported elsewhere.

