### Cluster randomisation

In each state, pharmacies were randomised to either Pharmacist Care Group (PCG) or Usual Care Group (UCG) according to the PhARIA. Randomisation was carried out at the pharmacy level to avoid the contamination likely to result from the same pharmacy recruiting and following up both intervention and control group patients. Randomisation was carried out at a central location using the sealed opaque envelope technique. To check for any 'Hawthorne effect' [20,21] in the UCG due to the effect of data collection, a third group of patients (Hidden Control Group - HCG) who are taking or have taken antihypertensives in the previous six months (but not included as participants in the UCG) will also be identified.

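### Paired tests are named for comparisons between independent groups (PCG vs UCG, UCG vs HCG), so the article states no usable test of the intervention effect

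*Protocol article*

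**What the plan says.** All places cited are in the protocol article.

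- **Main comparison (Data analysis).** The tests are given as "Paired t-tests and/or Wilcoxon Signed Rank test will be used to compare changes in total scores on the Morisky scale, TABS and MedsIndex between", and the sentence continues "between the PCG and the UCG at baseline and six months".
- **Hawthorne check (Data analysis).** "MedsIndex scores will be compared using paired t-tests and/or Wilcoxon Signed Rank test in the UCG and the HCG at six months".
- **How PCG and UCG arise (Cluster randomisation).** "In each state, pharmacies were randomised to either Pharmacist Care Group (PCG) or Usual Care Group (UCG) according to the PhARIA". The reason for using pharmacies is also given: "Randomisation was carried out at the pharmacy level to avoid the contamination". No patient therefore belongs to both groups.
- **Who the HCG are (Cluster randomisation).** They are users of antihypertensives, "but not included as participants in the UCG) will also be identified". The Abstract places them in the UCG pharmacies.
- **Other tests named (Data analysis).** Unpaired tests and a regression do appear: "Significant factors in univariate analysis (chi-square, Mann-Whitney U test and Student's t-test) will be further tested in multivariate analysis (linear regression"). They belong to a different task, introduced by "Baseline data will be used to identify factors associated with suboptimal adherence in the whole study population". The adjustment for pharmacy is attached to those regression models.
- **Sample size.** 182 per group, to detect 50% in the UCG against 65% in the PCG with 80% power and two-sided 0.05. That is a difference between groups.

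**The concern.** A paired t-test or signed-rank test needs two measurements on the same unit, or on units matched by design. PCG and UCG patients attend different pharmacies, HCG patients are by definition not UCG participants, and the article describes no matching. The only tests named for the primary outcome therefore do not fit the comparison they are meant to make.

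What is at stake is the randomised contrast. An analyst following the text must invent a pairing, substitute another test without support from the plan, or test each arm against its own baseline. The third route invites reading a significant change in one arm and a non-significant change in the other as evidence of benefit, which is not a test of the difference.

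A change common to both arms is plausible here. Recruitment favours patients with a lapsed or suboptimal refill record, so regression to the mean may occur, and the HCG exists because a Hawthorne effect in the UCG was foreseen.

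**Working it through.** **1. The plan's own figure.** Inputs from Sample size: 0.50 and 0.65, two-sided 0.05 (z = 1.960), power 0.80 (z = 0.842), mean proportion 0.575. For two independent proportions:

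n = [1.960·√(2 × 0.575 × 0.425) + 0.842·√(0.50 × 0.50 + 0.65 × 0.35)]² / 0.15² = 169.3

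With continuity correction: (169.3/4) × [1 + √(1 + 4/(169.3 × 0.15))]² = 182.4, against the stated 182 (183 if rounded up). The trial was sized for an unpaired comparison of two groups, which the Data analysis section does not name.

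**2. Reading A: pair across groups.** No pairs exist. With unequal numbers, for example 182 and 175, the paired test returns an error. With equal numbers and arbitrary pairing of unclustered data (20,000 simulated trials, 182 per arm, no effect), the rejection rate was 0.0498 for the paired and 0.0492 for the unpaired t-test. Pairing at random does not itself inflate type I error in that setting. The fault is that the p-value depends on an arbitrary ordering of patients and that the test is undefined for unequal arms.

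**3. Reading B: baseline against six months within each arm.** This can be computed, but its null hypothesis is no change over time in that arm. Nothing in it estimates PCG minus UCG. It is also unavailable for UCG against HCG, which is specified at six months only.

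**4. Size of the problem if Reading B is misused.** Assume no intervention effect, independent arms, and the same standardised change d (in SDs of the change score) in both. The article gives no value for d. Take 225 × 0.75 = 168.75, about 169 per arm, from the stated recruitment and drop-out. Let p be the power of each within-arm paired t-test, with non-centrality d·√169 = 13d. The chance of significance in the PCG but not the UCG is p(1 − p):

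| d | 13d | p | p(1 − p) |
|---|---|---|---|
| 0.10 | 1.30 | 0.253 | 0.19 |
| 0.15 | 1.95 | 0.492 | 0.25 |
| 0.20 | 2.60 | 0.734 | 0.20 |
| 0.30 | 3.90 | 0.972 | 0.027 |

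A 40,000-replicate simulation gave 0.188, 0.250 and 0.195 for the first three rows, and p = 0.973 for the fourth. With 182 per arm, the normal approximation gives 0.198, 0.249 and 0.018 at d = 0.10, 0.15 and 0.30. A valid two-sided 5% test would wrongly favour the PCG 2.5% of the time. The maximum of p(1 − p) is 0.25, at p = 0.5, so the range 0.10 to 0.20 lies around the worst case.

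**5. Adjusting for baseline rather than subtracting it.** With equal variances and baseline-to-follow-up correlation r, the variance ratio is (1 − r²)/[2(1 − r)] = (1 + r)/2. That is 0.75 at r = 0.5 and 0.85 at r = 0.7, so 25% and 15% lower variance. The values of r are assumptions.

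**The case against.** The best defence is that pairing refers to baseline and six months within a patient, as the mention of both time points suggests. That makes the first sentence workable, but it supplies no comparison between the arms, which the sentence says is its purpose, and it cannot explain the UCG-HCG sentence. Pairing pharmacy means is conceivable for UCG against HCG, since both come from the same pharmacies, but the text does not say so and it cannot apply to PCG against UCG.

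A second defence is that the test is simply mislabelled: the authors name unpaired tests in the next paragraph and sized the trial for independent groups. This may well be so. It makes the correction easy, but the method as stated is still wrong, and this is not detail left to an analysis plan.

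Three stronger readings are tempting and are not supported:

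- A reader might infer that the plan has a false-positive rate of 19-25%. It does not. Those figures require within-arm tests, a one-arm-only result read as efficacy, and a common change near the worst case. The article states none of these, and at 0.30 SD the figure is close to nominal.
- A reader might infer that baseline is ignored. It is not: changes in score are compared, so baseline enters by subtraction. Covariate adjustment is a gain in precision, not a repair of validity, and leaving the strata out of an article is ordinary condensation.
- A reader might infer that regression to the mean will occur on every measure. Selection is preferential and uses dispensing data; any carry-over to the self-reported scales is unknown.

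**Conclusion.** The point stands and should be corrected before analysis. The tests named for the primary PCG-UCG comparison and for the UCG-HCG check do not fit independent groups: across groups they are arbitrary or cannot be computed, and within arms they answer a different question. This rests on the text alone and needs no assumed figure.

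The size of the possible harm is conditional. Under the assumed misuse, no intervention effect, 169 per arm, independent arms and an assumed common change of 0.10 to 0.20 SD, a spurious PCG-only result would occur about 19-25% of the time, and about 3% at 0.30 SD. The choice of test does not alter the 182 per group, which already comes from an independent-groups formula. Whether that number suffices for clustering and drop-out is a separate matter.

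**What to change.** **PCG against UCG.** Replace the paired tests by a between-group model of the six-month score. Arm is the effect of interest; adjust for the baseline value of the same measure and for the randomisation strata (state and PhARIA category), and include a random pharmacy effect because pharmacies were randomised. Report the PCG-UCG difference with a 95% CI. A two-sample t-test or Mann-Whitney test on patients alone would not suffice, because it ignores the clustering.

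**UCG against HCG.** Use an unpaired comparison of six-month MedsIndex that accounts for the two groups sharing pharmacies. Adjust for baseline MedsIndex only if it can be derived from the HCG refill history; the Data analysis section mentions six months only, so its availability should be confirmed first.

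**Within-arm tests.** Keep paired tests of baseline against six months as description only, and state that they are not evidence of an intervention effect.

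**Cost.** Rewording of the Data analysis section and slightly more analysis work. The PCG-UCG change needs no new data, since both groups are measured at baseline and six months.

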### Recruitment of patient participants

A software application, MedeMine CVD, has been installed on the dispensing computer of participating pharmacies. MedeMine CVD extracts data from the market leading pharmacy dispensing software system in Australia (FRED Dispense^®^) and identifies patients who are using or have used antihypertensive medicines in the previous six months. The purpose of MedeMine CVD is to:

1. preferentially identify patients who last had their antihypertensive medications dispensed more than 59 days previously and those with suboptimal refill adherence;

2. generate personalised "Expression of Interest" (EOI) forms to mail to potential patient participants. Once the completed EOI has been received by the pharmacist and eligibility is confirmed, the information is recorded in MedeMine CVD;

3. generate the participant explanatory statement and consent form, as well as a letter and fax-back form to be sent to the participant's GP to confirm diagnosis of primary hypertension and advise of the participant's target BP;

4. manage participant appointments by pharmacists;

5. create a unique identification number for each participant, which is printed on all study documents (e.g. data collection forms and letters); and

6. send SMS reminders or prompt the pharmacist to telephone or send mail reminders, to participants who have requested this part of the service, when their supplies are dwindling.

An invitation letter (EOI) with a short questionnaire (seeking information about the patient's BP, interest in participation, nominated GP, including contact details and consent to contact the GP, and patient telephone contact details) and a reply-paid envelope were sent to potential participants. Patients were asked to return the completed questionnaire to the pharmacy and indicate their interest in participating. Once the EOI is received, the pharmacist will contact the patient to further assess their eligibility and arrange a mutually convenient time to visit the pharmacy to enrol in the study. If eligibility is confirmed, the consent form would then be signed. The pharmacist will also contact the patient's GP. At no point are patients' identities made known to the researchers.

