### Data collection

### Baseline visit

During the baseline visit to the pharmacy, the pharmacist will measure the patient's BP using a digital BP monitor (average of two readings as per WHO MONICA [23] and EHRM [24] protocols - if these differ by more than 5 mmHg, a third reading will be taken and the average of the two closest readings will be recorded). Each pharmacy has been provided with a BP monitor. The MedsIndex score will be calculated for each antihypertensive medicine the patient uses. Adherence will be measured using self-report tools - the Morisky scale and the TABS. The Beliefs and Behaviour Questionnaire [17] will be used to assess patient experiences, attitudes and beliefs regarding their health and treatment and the 8-item short Assessment of Quality of Life (AQoL) [25] will be used to measure health-related quality of life. The pharmacist will also collect information on the patient's medications and their understanding of and ability to use these medications. The PCG will also receive the intervention described earlier.

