### Six-month visit (Final project visit)

Measures performed at baseline will be repeated for both UCG and PCG patients at their six-month visit to the pharmacy.

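### The PCG-UCG comparison of raw changes in Morisky, TABS and MedsIndex leaves out the baseline score as a covariate, although it is collected in both arms, and so gives up precision

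*Protocol article*

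**What the plan says.** The Data analysis section names paired t-tests and/or the Wilcoxon signed rank test. Their stated task is this: "compare changes in total scores on the Morisky scale, TABS and MedsIndex between the PCG and the UCG at baseline and six months". These three instruments are the article's primary outcome measures. No covariate is given for this comparison. The only stated use of baseline data for comparing the arms is descriptive: "Participant characteristics in the UCG and PCG will be compared at baseline".

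The baseline scores exist. Under Baseline visit: "Adherence will be measured using self-report tools - the Morisky scale and the TABS", and "The MedsIndex score will be calculated for each antihypertensive medicine the patient uses". Under Six-month visit: "Measures performed at baseline will be repeated for both UCG and PCG patients at their six-month visit to the pharmacy".

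The only regression in the section has another purpose: "Baseline data will be used to identify factors associated with suboptimal adherence in the whole study population". The pharmacy variable is added to those predictor models. Study arm is not mentioned in them, so they do not supply a baseline-adjusted arm comparison.

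**The concern.** Subtracting the baseline score fixes the slope of the six-month score on baseline at 1. With equal SDs the best slope is rho, the correlation between the two measurements, and a covariate model estimates the slope from the data. When rho is below 1, the change score over-corrects: an arm that happens to start worse shows a larger raw improvement with no help from the intervention.

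Two things are at stake. The first is precision on the primary outcome measures. The second is how a chance baseline difference is read. Cluster randomisation and the Abstract put 56 pharmacies, not individual patients, into the randomisation, so some difference between arms at baseline is to be expected.

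The point is separate from the choice of a paired test and from the lack of a cluster adjustment in the arm comparison. Correcting both of those would still leave a raw change score.

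**Working it through.** **Inputs from the article.** Sample size section: 182 evaluable patients per group, two-sided 0.05, 80% power, 50% v 65% adherent. Abstract: 56 pharmacies.

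**Inputs assumed.** Rho is not given; 0.3 to 0.7 is shown. Baseline and six-month SDs are taken as equal, and scores are in SD units.

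**The article's own figure.** The usual two-proportion formula for 50% v 65% gives 170 per group without continuity correction and 183 with it, so the stated 182 reproduces to within one patient. It is a calculation for a binary endpoint. The article states no power for any score, so a continuous effect has to be assumed to show the size of the loss.

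**Illustrative effect.** Take the effect that gives 80% power on an unadjusted six-month score with 182 per group: d = (1.960 + 0.842) × √(2/182) = 2.802 × 0.105 = 0.294 SD.

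**Standard errors and power.**
- Change score: SE = √(2/182) × √(2(1-rho))
- Baseline-adjusted: SE = √(2/182) × √(1-rho²)
- Power = Φ(d/SE - 1.960)

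| rho | 2(1-rho) | 1-rho² | Power, change | Power, adjusted |
|---|---|---|---|---|
| 0.3 | 1.40 | 0.91 | 66% | 84% |
| 0.4 | 1.20 | 0.84 | 73% | 86% |
| 0.5 | 1.00 | 0.75 | 80% | 90% |
| 0.6 | 0.80 | 0.64 | 88% | 94% |
| 0.7 | 0.60 | 0.51 | 95% | 97.5% |

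The variance ratio, adjusted over change, is (1-rho²)/(2(1-rho)) = (1+rho)/2. This is below 1 for every rho below 1, and is 0.75 at rho 0.5. Below rho 0.5 the change score has a larger variance than the six-month score alone, because 2(1-rho) exceeds 1.

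**Sensitivity to calibration.** If the effect is instead set so that the change score has 80% power, the adjusted analysis has 93.5% at rho 0.3, 89.9% at 0.5 and 86.0% at 0.7. The gap is then 13.5, 9.9 and 6.0 points.

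**Clustering.** Assume 28 pharmacies per arm, so 182/28 = 6.5 patients each, an ICC of 0.05, and the same design effect for both analyses: 1 + 5.5 × 0.05 = 1.275. At rho 0.5 and d = 0.294, power is 69.9% v 81.7%.

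**Chance imbalance.** If the arms differ at baseline by b SD, the change-score estimate moves by (1-rho) × b in favour of the arm that starts worse. For b = 0.1:
- rho 0.3: 0.07 SD, 0.07/0.294 = 24% of the illustrative effect
- rho 0.5: 0.05 SD, 17%
- rho 0.7: 0.03 SD, 10%

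A difference of 0.1 SD is about one standard error of the baseline difference even before clustering (√(2/182) = 0.105). A simulation at rho 0.5 gave a slope of -0.52 on the imbalance, against -0.5 expected, and a mean estimate near zero under no effect. This leak is not a second penalty on top of the power loss: 2(1-rho) - (1-rho²) = (1-rho)², which is exactly the extra variance in the table.

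**The case against.** The strongest reply is that this is a choice about efficiency and not an error. With baseline differences due to chance, a properly executed change-score comparison is unbiased on average and keeps its type I error. That stands. A reader might infer that the planned comparison is biased, or that any baseline imbalance turns wholly into apparent effect. Neither follows: only the fraction 1-rho leaks, and it averages to zero over randomisations.

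Second, the sentence has a more basic defect. Its tests are paired and cannot compare two independent arms, and whoever rewrites it would choose covariates then. That is a reason to make both edits together, but replacing the test does not by itself bring in the baseline score. Nor is this an omission that an article may leave to a fuller plan, since the text states that changes are compared.

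Third, the power figures rest on an assumed rho and an assumed continuous effect. This also stands. A reader might infer that the trial's stated 80% falls by 10 points. The documents do not support that, because the 80% belongs to a binary comparison. Moreover, at rho 0.5 the illustrative change score is itself at 80%, so what is lost is an available gain. The Primary outcome measures section gives no look-back period for MedsIndex; overlapping refill history would raise rho and shrink the gain. Morisky has four yes/no items and MedsIndex is capped at 100, so normal-theory figures are only a guide. Stable differences between pharmacies cancel in a change score, so a common design effect is a simplification too.

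Fourth, recruitment is meant to "preferentially identify patients who last had their antihypertensive medications dispensed more than 59 days previously and those with suboptimal refill adherence", and a reader might infer that regression to the mean alone will produce a spurious effect. The same selection runs in both arms, so that upward drift is shared and cancels on average; only a difference between arms matters.

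Finally, a reader might infer that adjustment removes all trouble from imbalance. It need not. Pharmacists enrol their own patients, and PCG pharmacists were offered Phase II training before baseline data collection, so differences could be systematic.

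**Conclusion.** The point holds as a matter of precision and of robustness to chance imbalance. The article fixes an unadjusted comparison of changes for its primary instruments while collecting, in both arms, the baseline scores needed for a better one. Given equal SDs, the direction does not depend on rho: the adjusted analysis has (1+rho)/2 of the change-score variance, a cut of 35% at rho 0.3, 25% at 0.5 and 15% at 0.7. The power gap on the illustrative effect runs from about 18 points at rho 0.3 to about 2.5 at rho 0.7, and depends on the calibration. It assumes continuous scores with equal SDs and says nothing about power for 50% v 65%.

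The change-score comparison is not shown to be invalid, and adjustment reduces but does not guarantee removal of bias from systematic recruitment differences.

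**What to change.** In Data analysis, when the paired tests are replaced by a between-arm, cluster-aware model, write it as a model of the six-month score on study arm with that instrument's own baseline score as covariate, separately for Morisky, TABS and MedsIndex. MedsIndex is scored per medicine, so the baseline covariate should be the same per-patient summary as the outcome. If the percentage adherent is tested, include baseline adherence status or score in that model as well. Report the adjusted arm difference with its 95% CI and keep raw change as a descriptive summary only.

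The cost is one sentence. No new data, visits or patients are needed. The downside is one covariate per model and a stated rule for missing baseline scores; a change score would lose those patients too.

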**Methods/Design:**

The HAPPY trial is a multi-centre prospective randomised controlled trial. Fifty-six pharmacies have been recruited from three Australian states. To identify potential patients, a software application (MedeMine CVD) extracted data from a community pharmacy dispensing software system (FRED Dispense^®^). The pharmacies have been randomised to either 'Pharmacist Care Group' (PCG) or 'Usual Care Group' (UCG). To check for 'Hawthorne effect' in the UCG, a third group of patients 'Hidden Control Group' (HCG) will be identified in the UCG pharmacies, which will be made known to the pharmacists at the end of six months. Each study group requires 182 patients. Data will be collected at baseline, three and six months in the PCG and at baseline and six months in the UCG. Changes in patient adherence and persistence at the end of six months will be measured using the self-reported Morisky score, the Tool for Adherence Behaviour Screening and medication refill data.

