### Ethics

This project has been approved by the Human Research Ethics Committees of Monash University, Curtin University and The University of Melbourne, and the Human Research Ethics Network of Tasmania. All pharmacists and patient participants (in the UCG and PCG) provided written informed consent at the time of enrolment.

Approval to access dispensing data for the HCG was given on the basis that pharmacists have routine access to this data about their patients via the dispensing program and would use it in normal practice to routinely check their patient's history for actual or potential medication-related problems. The researchers will have access only to deidentified patient data.

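### The Hawthorne check compares non-randomised UCG and HCG patients on six-month MedsIndex alone, so any pre-existing refill difference is mixed with the effect it is meant to detect

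*Protocol article*

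**What the plan says.** All references are to the protocol article.

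- **Analysis.** Data analysis gives one UCG-HCG comparison: "MedsIndex scores will be compared using paired t-tests and/or Wilcoxon Signed Rank test in the UCG and the HCG at six months". The sentence before it, on the Pharmacist Care Group (PCG) and the UCG, names two time points: "TABS and MedsIndex between the PCG and the UCG at baseline and six months". The planned comparison of baseline characteristics covers the UCG and PCG only.
- **Who is in the HCG.** Cluster randomisation describes current or recent users of antihypertensives ("but not included as participants in the UCG) will also be identified"). The Abstract adds where they come from and when they are revealed: "will be identified in the UCG pharmacies, which will be made known to the pharmacists at the end of six months".
- **Who is in the UCG.** Recruitment of patient participants says the software is there to "preferentially identify patients who last had their antihypertensive medications dispensed more than 59 days previously and those with suboptimal refill adherence". Then: "Patients were asked to return the completed questionnaire to the pharmacy and indicate their interest in participating". Inclusion and Exclusion criteria add, among others, a diagnosis of primary hypertension and self-administration. Ethics adds consent: "All pharmacists and patient participants (in the UCG and PCG) provided written informed consent at the time of enrolment".
- **Access to HCG data.** Ethics: "Approval to access dispensing data for the HCG was given on the basis that pharmacists have routine access to this data".

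**The concern.** The HCG exists to show whether taking part in data collection changes refill behaviour in the UCG. That inference needs the two groups to have had similar refill behaviour had nobody been observed. They are formed by different routes, no randomisation or matching between them is stated, and the comparison as written uses only the final score. A six-month gap could then be a Hawthorne effect, a difference that was there at the start, or both.

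The error can run either way. If people who volunteer and consent refill better than others, the UCG would look improved by observation. If targeting poor refillers dominates, the UCG would look worse and a real Hawthorne effect could be hidden. So neither a significant nor a null result has a clear meaning. The Abstract and the Discussion both present this control as a distinguishing feature of the trial, so the result is likely to be relied on.

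**Working it through.** **Step 1. The two groups side by side**

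| Step | UCG | HCG |
|---|---|---|
| Antihypertensive use in last six months | required (four named classes or combinations with them) | required (classes not stated) |
| Preferential flag: over 59 days since dispensing, or suboptimal refills | yes | not stated |
| Replied to mailed invitation | yes | not stated |
| Primary hypertension, self-administers | yes | not stated |
| Written consent | yes | none (consent covers UCG and PCG) |
| MedsIndex at baseline | yes (Baseline visit) | not stated |
| MedsIndex at six months | yes | yes |

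**Step 2. The plan's own sample size**

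The Hawthorne check has no sample size of its own. The Abstract gives 182 per study group after describing three groups. Sample size gives 182 for 50% versus 65%, 80% power, two-sided 0.05.

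n = [1.96·√(2·0.575·0.425) + 0.8416·√(0.5·0.5 + 0.65·0.35)]² / 0.15² = (1.370 + 0.582)² / 0.0225 = 169.3, so 170 per group.

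With continuity correction: (169.3/4)·[1 + √(1 + 4/(169.3·0.15))]² = 182.4. The stated 182 is reproduced to within rounding, and I use it for both groups below.

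**Step 3. A pre-existing difference and no Hawthorne effect**

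Let g be the assumed UCG-HCG difference in SD units. The two-group test statistic is centred on g·√(182/2) = 9.539g, and the chance of significance is P(|Z| > 1.96).

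| g | centre | P(significant) |
|---|---|---|
| 0.1 | 0.954 | 16% |
| 0.2 | 1.908 | 48% |
| 0.3 | 2.862 | 82% |

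The sign of g does not matter. Clustering is ignored.

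**Step 4. Refill targeting, and what each analysis does with it**

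Assume standard normal scores with baseline to six-month correlation ρ. Let the UCG come from the lower half of baseline scores and the HCG from everyone, with no Hawthorne effect. The lower half has mean −√(2/π) = −0.798. The expected six-month difference is −0.798ρ, which is −0.24, −0.40 and −0.56 at ρ = 0.3, 0.5 and 0.7. The expected difference in change is +0.798(1−ρ), which is +0.56, +0.40 and +0.24.

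A simulation (1,500 runs, 182 per group, no Hawthorne effect) gives the same differences. Each cell shows the mean difference in SD and the rejection rate; the last column is the rejection rate only.

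| Assumed setting | Six-month only | Change score | Baseline-adjusted |
|---|---|---|---|
| No selection, ρ=0.5 | 0.00; 5.3% | 0.00; 5.7% | 5.5% |
| UCG lower half, HCG unselected, ρ=0.3 | −0.24; 62.7% | +0.56; 99.9% | 5.3% |
| same, ρ=0.5 | −0.40; 96.7% | +0.40; 97.5% | 5.1% |
| same, ρ=0.7 | −0.56; 100% | +0.24; 83.7% | 5.4% |
| Both from lower half, ρ=0.5 | 0.00; 4.9% | 0.00; 5.8% | 5.2% |
| Volunteer difference 0.3 SD only, ρ=0.5 | +0.30; 79.1% | 0.00; 5.1% | 35.7% |
| Both lower half, volunteer 0.3, ρ=0.5 | +0.20; 52.0% | +0.10; 15.6% | 33.9% |
| UCG lower half, volunteer 0.3, HCG unselected, ρ=0.5 | −0.20; 51.8% | +0.50; 99.9% | 32.5% |

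Selection on baseline refills is handled by adjustment for baseline and not by a plain change score. A volunteer difference survives the adjustment: rejection is still about one in three at 0.3 SD. The change score does better in the two settings where refill selection is the same in both groups, but fails badly once it differs.

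**The case against.** **The article is condensed.** It does not say how HCG patients are sampled, and the full protocol might apply the same software rules or match the groups. This stands in part. A reader might infer that the HCG consists of non-flagged patients, non-responders, decliners and ineligible people. The definition permits all of these, but the document does not say in what proportion, or that the flag was not used. It does show that no HCG patient went through the UCG's consent step, and it fixes the analysis at one time point.

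**The word paired may hint at a baseline.** A paired test has no meaning for two different sets of patients at one time, so a within-group comparison of baseline with six months might be meant. That needs a baseline HCG score, which is not mentioned, and separate within-group tests give no UCG-HCG contrast. The preceding sentence names both time points where both are intended.

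**Regression to the mean.** A reader might infer that it is the main fault of the planned contrast. It is not: in a six-month-only comparison it shrinks a selection difference. It mainly distorts change scores, which matters for the choice of remedy.

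**Direction.** A reader might also infer that volunteers refill better. The document has no figure or source for that, so it stays an assumption.

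**The figures are generic.** Correct. The 16%, 48% and 82% hold for any two groups of 182 at those differences. They show sensitivity, not that a bias of this size exists. The lower-half selection in Step 4 is also stricter than preferential flagging.

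**Conclusion.** The point holds for the plan as written. The UCG-HCG comparison is a non-randomised, single-time contrast between groups formed differently, so a six-month MedsIndex difference, or its absence, cannot be attributed to a Hawthorne effect or its absence.

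The size is unknown because the document gives no UCG-HCG difference, SD or correlation. Under assumed differences of 0.1 to 0.3 SD, 182 per group and no clustering, false significance occurs in 16% to 82% of trials instead of 5%. The size of the HCG is itself an assumption: the totals under Sample size cover two groups only (2 × 225 = 450).

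A reader might conclude that the trial's main result is compromised. It is not: the randomised PCG-UCG comparison does not use the HCG, and the check is not listed among the primary or secondary outcomes. Nor would a baseline score alone make the check sound, since volunteer and eligibility selection would remain. The change is worth making because the check is promoted as a strength and can be improved before HCG data are extracted.

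**What to change.** 1. Derive MedsIndex for each HCG patient at the date corresponding to UCG baseline as well as at six months. The score is computed from refill history, so no visit is needed and the group can stay hidden. First check that the ethics approval covers the earlier date.
2. Compare six-month MedsIndex between UCG and HCG with an unpaired model adjusted for baseline MedsIndex and accounting for pharmacy (for example, a random pharmacy intercept). Do not use a plain change-score comparison as the analysis.
3. Draw the HCG within each UCG pharmacy by the dispensing-based rules used for the UCG: the same drug classes and the same refill and 59-day flag.
4. Record whether each HCG patient was mailed an invitation. Using the same flag brings in patients who may have been invited and not enrolled, so this is needed for interpretation.
5. Report the contrast as non-randomised, with residual volunteer and eligibility selection. GP-confirmed diagnosis and self-administration are not shown to be available in dispensing data.

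The cost is one further score per HCG patient and some extra data handling. The article does not say whether the installed software can export past MedsIndex values or rebuild past flag status, so this should be confirmed first. The PCG-UCG analysis does not change.
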